## Abstract

**Background:**

Patients with resected oral cavity squamous cell carcinoma (OCSCC) are often treated with adjuvant radiation (RT) ± concomitant chemotherapy based on pathological findings. Standard RT volumes include all surgically dissected areas, including the tumour bed and dissected neck. RT has significant acute and long-term toxicities including odynophagia, dysphagia, dermatitis and fibrosis.

The goal of this study is to assess the rate of regional failure with omission of radiation to the surgically dissected pathologically node negative (pN0) hemi-neck(s) compared to historical control, and to compare oncologic outcomes, toxicity, and quality of life (QoL) profiles between standard RT volumes and omission of RT to the pN0 neck.

**Methods:**

This is a multicentre phase II study randomizing 90 patients with T1–4 N0–2 OCSCC with at least one pN0 hemi-neck in a 1:2 ratio between standard RT volumes and omission of RT to the pN0 hemi-neck(s). Patients will be stratified based on overall nodal status (nodal involvement vs. no nodal involvement) and use of concurrent chemotherapy. The primary endpoint is regional failure in the pN0 hemi-neck(s); we hypothesize that a 2-year regional recurrence of 20% or less will be achieved. Secondary endpoints include overall and progression-free survival, local recurrence, rate of salvage therapy, toxicity and QoL.

**Discussion:**

This study will provide an assessment of omission of RT to the dissected pN0 hemi-neck(s) on oncologic outcomes, QoL and toxicity. Results will inform the design of future definitive phase III trials.

**Trial registration:**

Clinicaltrials.gov identifier: NCT03997643. Date of registration: June 25, 2019, Current version: 2.0 on July 11 2020.

## Background

Patients with resected squamous cell carcinoma of the oral cavity (OCSCC) are at risk of locoregional failure recurrence (LRR), at either the tumour surgical bed or in the neck. Postoperative radiotherapy (PORT) is often added after surgical resection to reduce the risk of local and regional recurrence in patients with high-risk features. Guidelines generally recommend PORT in patients with more than one lymph node involved, pT3 or pT4 primary disease, lymphovascular invasion (LVI), perineural invasion (PNI), close or positive margins, extranodal extension (ENE), and sometimes for patients with lymph node involvement of neck levels IV or V [1–4].

ENE and positive surgical margins are considered the highest-risk pathological features, whereas the other adverse features are considered ‘intermediate risk’. Patients with high-risk features are generally offered concurrent chemotherapy with PORT, based on a post-hoc analysis two of randomized trials [5–7]. In patients with other adverse features, there is limited randomized evidence of the benefits of PORT alone [8–10]. Retrospective series and comparisons with historical controls have shown reductions in LRR and improvement in overall survival (OS) with PORT [11–18].

RT treatment volumes after surgery generally include the entire surgical bed, including the dissected hemi-neck(s), and may include the contralateral undissected neck at the discretion of the treating physician [19]. However, PORT is associated with significant acute and late toxicities, including dysphagia, mucositis, xerostomia, dermatitis, fibrosis, osteoradionecrosis, voice changes, ototoxicity and hypothyroidism [7, 20]. Larger RT treatment volumes are associated with increasing toxicity. These large treatment volumes are based on historical practice, without guidance from randomized evidence. The benefit of treating the nodal regions in the pathologically node negative (pN0) neck is unknown.

Retrospective studies looking at series of oral cavity cancer patients in whom PORT was omitted altogether have also demonstrated low rates of isolated nodal recurrence ranging from 8 to 15% [21–23]. In their series of 166 patients with mostly T1-T2 oral tongue tumours with a pN0 neck treated with surgery alone (75%), PORT to the primary site (8%) or PORT to the primary site and neck (17%), So et al. reported a rate of isolated nodal recurrence of 7–8% in all groups [21]. Mizrachi et al. described a series of 558 patients with T1-T4 disease and pN0 neck with 65% not receiving PORT, with a neck recurrence rate of 10% [22]. In Ganly et al., 164 patients with pT1-T2 pN0 oral tongue cancer without PORT had an isolated regional recurrence rate of 15%, with an additional 5% having a simultaneous locoregional recurrence. In this study depth of invasion was predictive of neck recurrence [23]. In a series of 127 patients with a pN1 neck, the neck recurrence-free survival was 85% in those receiving PORT vs 84% in those without PORT [24]. It is difficult to draw comparisons between groups receiving or not receiving PORT in these retrospective studies since those receiving PORT had more risk features.

Retrospective data from a small number of PORT volume studies also demonstrate good oncologic outcomes in patients where radiation was omitted to the contralateral clinically or pathologically N0 neck [25, 26]. In Vegeer et al. 123 patients with well-lateralized oral cavity or oropharynx squamous cell carcinoma (SCC) were treated with unilateral PORT, with 60% of patients N0 and 41% N1 or N2. Contralateral metastases developed in only 6% of patients, with most successfully receiving salvage therapy [25].

A recent non-randomized prospective phase II trial eliminated PORT to the pN0 neck in 72 patients with head and neck squamous cell carcinoma (HNSCC), demonstrating excellent results with no isolated failures and 97% control in the unirradiated pN0 neck. Twenty percent of patients included in the study had oral cavity tumours [27].

Taken together, the existing retrospective and prospective data suggests that omitting PORT in patients with a pN0 neck likely has a recurrence rate less than 15–20%. However, no randomized studies have directly examined the omission of PORT in the pN0 neck. There is also a paucity of data examining the effects of omission of PORT on QoL. We hypothesize that omitting PORT to the hemi-neck(s) that have been dissected and shown to be pN0 will be associated with acceptable rates of regional recurrence and will improve quality of life (QoL). The goal of this randomized phase II study is to assess oncologic outcomes, functional outcomes, and QoL in patients treated with PORT to the historically standard volumes (usually including the primary site and all dissected neck areas) vs. PORT only to the primary site and pathologically involved hemi-neck, omitting radiation to the pN0 hemi-neck(s).

## Methods / design

### Objectives

The objectives of this trial are to:
Compare regional recurrence rate to historical controls with omission of PORT to the pN0 neck.Compare oncologic outcomes, toxicity and QoL for PORT (± chemotherapy) based on standard treatment volumes (including the primary site tumour bed, dissected neck ± elective nodal regions) vs. PORT [± chemotherapy] that avoids treating the dissected, pN0 neck.

It is generally accepted that a risk of nodal recurrence of 15–20% is sufficient to warrant radiation to a nodal basin. Our hypothesis is that for patients with SCC of the oral cavity, T1–4 N0–3 (as per AJCC 8th edition) with at least one surgically dissected pN0 hemi-neck, the regional failure rate will be 20% or less at 2 years when treated with PORT omitting the pN0 neck.

### Study design

This is an open-label phase II multi-centre randomized trial. Patients will be randomized between current standard of care treatment (Arm 1) vs. omission of radiation to the pN0 dissected hemi-neck(s) (Arm 2) in a 1:2 ratio (Fig. 1). The required sample size is 90 patients. Stratification factors include neck nodal status (pN0 vs pN+) and use of chemotherapy. Patients will be recruited from tertiary care centres (full list of participating sites available on clinicaltrials.gov, NCT03997643).

**Fig. 1 Fig1:**
[figure not shown]
Study schema

#### Primary endpoint

Regional failure in the pN0 hemi-neck(s)

#### Secondary endpoints

OSDisease-free survival (DFS)Local recurrenceRegional recurrenceLocoregional recurrenceRate of salvage treatment (surgery ± radiotherapy) in the pN0 neck, and freedom from unsalvageable neck recurrenceQoL at 1 year, assessed with the MD Anderson Dysphagia Inventory (MDADI) [28], the European Organisation for Research and Treatment of Cancer (EORTC) Quality of Life Cancer Patients general (QLQ-C30) [29] and head & neck (H&N35) scales [30], the EuroQOL 5-Dimension 5-Level (EQ-5D-5L) [31], and the Neck Dissection Impairment Index (NDII) [32]QoL measured at treatment completion and 6, 12, 15,18, 24, 30, 36, 42, 48, 54 and 60 months, measured with MDADI, EORTC QLQ-C30, H&N35, EQ-5D-5L and NDIIRate of feeding tube insertion after start of radiation (either gastric, gastrojejeunal, or nasogastric) and rate of feeding tube use at 1-year post-randomization.Swallowing function at 1-year, assessed by Modified Barium Swallow (MBS) study and measured by the Modified Barium Swallow Impairment Profile (MBSImP™©) score [33], the Dynamic Imaging Grade of Swallowing Toxicity (DIGEST™) score [34], and the Functional Oral Intake Scale (FOIS) [35].Toxicity, assessed using the National Cancer Institute Common Toxicity Criteria (NCI-CTC) version 4.03Rate of failure in the clinically node negative neck, if applicable (i.e. the undissected node-negative neck, for well-lateralized tumours).

#### Inclusion criteria

Age 18 years or olderWilling to provide informed consentEastern Cooperative Oncology Group (ECOG) performance status 0–2Resected OCSCC with at least an ipsilateral selective neck dissection. The oral cavity includes: lips, buccal mucosa, oral tongue, floor of mouth, gingiva, retromolar trigone, and hard palatePatient has at least one pathological feature that is an indication for PORT: positive or close (≤ 3 mm) margin, presence of LVI or PNI, pT3 or pT4 disease, positive lymph nodes, or ENEPORT is recommended by the treating physicianPathologically lymph node negative in at least one dissected hemi-neck with at least 10 nodes recovered in each pN0 hemi-neck, after a dissection that at minimum includes nodal levels 1–3 in the pN0 hemi-neck(s).Radiation contours have been peer-reviewed and approved

#### Exclusion criteria

Patients with an ipsilateral neck dissection only with positive lymph nodes, unless they undergo a contralateral neck dissection that is pN0Patients with bilaterally involved neck nodesPatients with pT3-T4 tumours **involving midline** who undergo an ipsilateral neck dissection (unless a contralateral neck dissection is performed)Serious medical comorbidities or other contraindications to radiotherapyPrior history of head and neck cancer within 5 yearsAny other active invasive malignancy, except non-melanotic skin cancers, low-risk prostate cancer, and Stage I-IVA papillary or follicular thyroid cancer.Prior head and neck radiation at any timePrior oncologic head and neck surgery in the oral cavity or neck.Known metastatic diseaseLocoregional disease recurrence identified following surgical resection but prior to start of radiotherapyInability to attend full course of radiotherapy or follow-up visitsUnable or unwilling to complete QoL questionnairesPregnant or lactating women

#### Pre-treatment evaluation

History and physical examination by a radiation oncologist within 5 weeks prior to randomizationStaging prior to randomization:
◦ CT or MRI of the neck (with contrast unless contraindicated) within 14 weeks of randomization. This can include the pre-operative CT, or the radiation therapy CT or MRI simulation if reviewed by a radiologist.
▪ In some instances, suspicious lymph nodes are visible on the scan after surgery. In such instances, recurrence must be ruled out pathologically before enrollment, either with a needle biopsy or resection of these nodes.◦ CT of the chest or whole body PET-CT (usually prior to surgery, must be within 14 weeks of randomization)Histological confirmation of SCCPregnancy test for women of child-bearing age within 2 weeks of randomizationDental evaluation prior to starting treatment, except edentulous patientsAssessment of dysphagia using NCI-CTC version 4.03 within 2 weeks of treatment initiationCompletion of QoL scoring prior to initiation of treatmentPrior to randomization, radiation contours are to be peer-reviewed and approvedMBS at baseline prior to initiation of treatment with documentation of the MBSIimP™©, DIGEST™ and the FOIS scores

#### Treatment plan

Surgical resection, and adjuvant radiotherapy and chemotherapy will be delivered in accordance with National Comprehensive Cancer Network (NCCN) Clinical Guidelines [1].

Primary tumours should be resected en bloc whenever possible with the goal of achieving clear margins. Patients with midline involvement of the primary tumour should receive a bilateral neck dissection.

Adjuvant cisplatin-based chemotherapy concurrent with radiotherapy is at the discretion of the treating medical oncologist, and is recommended for patients with positive margins or ENE (for patients who can tolerate chemotherapy). For patients who are deemed unfit or too elderly (> 70 years of age) for cisplatin-based chemotherapy, the standard dose and/or schedule can be modified, alternative systemic therapy regimens maybe used (eg. weekly carboplatin, Calais regimen), or systemic therapy can be omitted at the discretion of the treating physicians. It is strongly recommended that radiation starts within 6 weeks of the date of surgery, and it is mandatory to start no more than 7 weeks after the date of surgery.

During treatment, supportive care should be in accordance with local standard of care, which often includes speech language pathology (SLP) assessment. Any SLP interventions (e.g. providing swallowing exercises) should be the same in both arms and conform to local standard of care.

##### Dose/fractionation

In both arms, a dose of 60 Gy in 30 fractions will be delivered to the operative bed target volumes. Centres that normally treat dissected, node-negative levels to 54 Gy in 30 fractions will be permitted to do so, if used consistently for all patients on trial. Areas of positive margins or ENE should receive 64 Gy in 30 fractions if those areas can be localized. Undissected areas that require coverage, in the opinion of the treating radiation oncologist (e.g. low neck, retrostyloid space), should receive 54 Gy in 30 fractions (Table 1).

**Table 1 Tab1:** Radiation treatment volumes and doses

PTV Volume	CTV Volumes Included		Dose in 30 fractions
	Arm 1	Arm 2	
**PTV64** Areas of positive margin or ENE	CTV64	CTV64	64 Gy
**PTV60** Dissected neck	CTVp60 CTVn60pos CTVn60neg	CTVp60 CTVn60pos	60 Gy
**PTV54** **(optional)** Not surgically dissected elective nodal regions	CTVn54pos CTVn54neg	CTVn54pos	54 Gy

##### Immobilization and localization

All patients will be immobilized in a custom thermoplastic shell and will undergo a planning CT simulation (with or without IV contrast) encompassing the head and neck to below the clavicles. The planning CT will be fused with other diagnostic imaging (e.g. MRI scans or pre-operative CT) where necessary. Bite blocks / tongue depressors / jaw separators may be used as per institutional protocol; these must be determined at the time of planning CT, prior to contour generation and patient randomization.

##### Radiotherapy volume definitions

A randomization volume will be defined as the nodal volume in the dissected pN0 hemi-neck(s). The randomization volume will depend on the laterality of the neck dissection performed (ipsilateral vs. bilateral), and whether pathologically involved nodes are present in the neck dissection, defined in Fig. 2. Patients with bilaterally involved neck nodes are ineligible. Patients with a unilateral neck dissection with positive lymph nodes are ineligible unless they undergo a staged neck dissection of the opposite side that is pN0.

**Fig. 2 Fig2:**
[figure not shown]
The “Randomization Volume” corresponds to the pN0 hemi-neck(s). The neck volumes included in the “Randomization Volume” depend on whether the patient had an ipsilateral vs. bilateral neck dissection, and the pathological findings in each hemi-neck(s). Patients with bilaterally involved neck nodes are ineligible. Patients with an ipsilateral neck dissection with positive lymph nodes are ineligible unless they undergo a contralateral neck dissection that is pN0. If randomized to standard treatment volumes (Arm 1), all contoured volumes, including the “Randomization Volume” will be treated. If randomized to omission of the pN0 neck (Arm 2), the “Randomization Volume” will be omitted from treatment planning

**Standard treatment volumes (Arm 1):** If randomized to Arm 1, all contoured volumes, including the randomization volume will be treated.

**Omission of pN0 neck (Arm 2):** If randomized to Arm 2 the randomization volume will be omitted from treatment planning.

**Clinical Target Volumes (CTV):**

The following radiation volumes will be contoured for all patients prior to randomization (Table 1). The suffix “pos” denotes CTVs in the node-positive hemi-neck, and the suffix “neg” denotes the CTVs in the node-negative hemi-neck.
**High-risk volume (CTV64):** regions corresponding to positive margins or ENE, if present, and if those areas can be localized.**Primary tumour operative bed (CTVp60):** surgically dissected areas corresponding to the resected primary tumour, typically including the pre-operative tumour area and any flap reconstructions and clips with a margin.**Involved neck:**
**Surgically dissected involved neck nodal volume (CTVn60pos):** surgically dissected neck levels in the node-positive hemi-neck, if applicable. In the dissected neck, some centres routinely treat only involved nodal areas to 60 Gy and the remainder of the dissected neck to 54 Gy. For centres where this is standard, this approach is acceptable, but all patients enrolled from these centres must be treated with this approach. The areas treated to 54 Gy would be included in a CTVn54pos.**Optional uninvolved low-risk neck on the involved side (CTVn54pos):** low-risk undissected neck nodal volume on the involved side, if applicable at the discretion of the radiation oncologist. This may include the standard lymphatic drainage sites not dissected at the time of surgery in the node positive hemi-neck such as the nodal levels below or above the dissected areas (e.g. level IVb, retrostyloid space).**“Randomization Volume” corresponding to the Uninvolved neck:**
**Surgically dissected involved neck nodal volume (CTVn60neg):** surgically dissected neck levels in the node negative hemi-neck. In centres that routinely treat the pN0 neck to 54 Gy, that dose is acceptable, but all patients must be treated with that approach. In such centres, these areas treated to 54 Gy would be included in a CTVn54neg.**Optional uninvolved low-risk neck on the uninvolved side (CTVn54neg):** low-risk undissected neck nodal volume on the uninvolved side, if applicable at the discretion of the radiation oncologist. In a patient who has had a unilateral neck dissection that was pN0, this may include the contralateral clinically node negative (cN0) neck if that is standard institutional practice

If randomized to omission of PORT to pN0 neck (Arm 2), the CTVn60neg and CTV54neg contours are deleted after randomization, prior to treatment planning. To prevent bias, contours cannot be changed after randomization. Local peer review of contours must take place before randomization occurs. An overview of the protocol timeline is shown in Fig. 3.

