#### Measurement of outcomes

**pN0 neck failure:** measured as time from randomization until disease recurrence in the initially pN0 hemi-neck(s). Patients with prior or simultaneous recurrence at the primary site or in the initially pN+ hemi-neck will be censored for this outcome as of that timepoint. The primary endpoint is a comparison of pN0 neck failure in Arm 2 vs. historical controls; this endpoint will also be compared between the two arms as a secondary endpoint.**OS:** measured as time from randomization until death from any cause.**DFS:** measured as time from randomization to either recurrence at any location or death, whichever occurs first. New primary tumours will not count as DFS events.**Local recurrence:** measured as time from randomization until disease recurrence at the primary site.**Regional recurrence:** measured as time from randomization until disease recurrence anywhere in the neck.**Locoregional recurrence:** measured as time from randomization until disease recurrence anywhere in the neck or at the primary site, whichever occurs first.**Recurrence in the pN0 neck without other locoregional recurrence:** measured as time from randomization until disease recurrence in the pN0 neck alone without recurrence at the primary site or pN+ neck.**Rate of salvage surgery and/or radiation in pN0 neck:** measured as time from randomization to salvage intervention (surgery ± radiation) in the pN0 neck. Freedom from unsalvageable neck recurrence will be reported as the time from randomization to development of a neck recurrence in the pN0 neck that could not be salvaged.**Feeding Tube Insertion:** Rate of feeding tube insertion after start of radiation (either gastric, gastrojejeunal, or nasogastric) and rate of feeding tube use at 1-year post-randomization. Patients with feeding tubes inserted prior to randomization will be censored for this endpoint.**Rate of failure in the clinically node negative neck**: for patients who have unilateral neck dissections, the cN0 neck may be treated with radiation or observed, at the discretion of the treating oncologist (see section 6). This is measured as the time from randomization to failure in the cN0 neck, and will be reported for the whole group of patients who had unilateral dissections, and also stratified by whether radiation was delivered to that area.

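### The protocol contradicts itself on whether the undissected cN0 neck belongs to the randomized volume; as written, Arm 2 can withhold radiation from a region outside the primary endpoint, and the planned cN0 split is partly a split by arm

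*Protocol article*

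**What the plan says.** Four parts of the protocol article bear on this.

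- **Radiotherapy volume definitions:** "A randomization volume will be defined as the nodal volume in the dissected pN0 hemi-neck(s"). The Fig. 2 legend likewise equates the volume with the pN0 hemi-neck(s).
- **Clinical Target Volumes:** the entry for the randomization volume has two components. CTVn60neg is the dissected node-negative neck. CTVn54neg is described as "low-risk undissected neck nodal volume on the uninvolved side, if applicable at the discretion of the radiation oncologist", and for a patient with a unilateral pN0 dissection, "this may include the contralateral clinically node negative (cN0) neck if that is standard institutional practice".
- **Deletion rule and Table 1:** for Arm 2, "the CTVn60neg and CTV54neg contours are deleted after randomization, prior to treatment planning". Table 1 agrees, listing CTVn54neg for Arm 1 only. The slightly different spelling in the deletion rule is taken to mean the same contour.
- **Measurement of outcomes:** for patients with unilateral dissections, "the cN0 neck may be treated with radiation or observed, at the discretion of the treating oncologist". Failure in the cN0 neck is to be reported for all such patients and "also stratified by whether radiation was delivered to that area".

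The primary event is "measured as time from randomization until disease recurrence in the initially pN0 hemi-neck(s"), and "The primary endpoint is a comparison of pN0 neck failure in Arm 2 vs. historical controls". Failure in the cN0 neck is a separate secondary endpoint.

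**The concern.** The sections give three different answers to who decides whether the cN0 neck is irradiated. Under the volume definition it is not randomized at all. Under the contour list and deletion rule, allocation decides once it has been contoured. Under the outcomes section the oncologist decides, with no mention of arm. Centres relying on different sections could deliver different Arm 2 treatments.

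Two statistical consequences follow if the deletion rule is applied as written:

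1. In some patients Arm 2 omits more than the primary endpoint observes. Only the primary endpoint carries the test that excludes a 20% failure rate, so that test says nothing about the extra region.
2. The split of cN0 failure by radiation delivered is neither a comparison of randomized groups nor a clean comparison of treated with untreated necks.

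**Working it through.** **1. Who is affected.** Patients with node-positive unilateral dissections are ineligible unless the other side is dissected and pN0. The affected patients therefore have a unilateral pN0 dissection and attend a centre that contours the contralateral cN0 neck. The article does not state their share, called f below.

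**2. What each arm receives in these patients, under the deletion rule.**

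| cN0 neck contoured before randomization | Arm 1 | Arm 2 |
|---|---|---|
| Yes | irradiated | contour deleted, not irradiated |
| No | not irradiated | not irradiated |

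Splitting by radiation delivered compares the single Arm 1/yes cell with the other three pooled. All irradiated cN0 necks are in Arm 1. The unirradiated group mixes Arm 2 patients whose contour was deleted with patients of either arm for whom cN0 treatment was never planned. The randomized comparison is along the first row.

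**3. Where a cN0 failure counts.** It is not a primary event, because an undissected neck is not pN0. It does count in cN0-neck failure, in regional recurrence (anywhere in the neck), in locoregional recurrence and in DFS.

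**4. The stated design reproduces.** Inputs from the Sample size section are 60 patients in Arm 2, 5% dropout, 80% unacceptable control, 92% target control and a one-sided 0.05 level.

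- Evaluable: 60 × 0.95 = 57.
- Success requires at least 51 of 57 controlled, that is, at most 6 failures. P(X ≥ 51 | 57, 0.80) = 0.0451, whereas P(X ≥ 50 | 57, 0.80) = 0.0934 exceeds 0.05.
- Power: P(X ≥ 51 | 57, 0.92) = 0.8313, matching the stated 83.1%.

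**5. Illustrative size.** Let c be the failure rate in the affected cN0 necks. The Background quotes 6% contralateral metastases after unilateral postoperative radiotherapy in well-lateralized tumours; 3% is an assumed lower value. All values of f are assumed. Expected cN0 failures in Arm 2 are 60 × f × c, from 60 × 0.10 × 0.03 = 0.18 to 60 × 0.75 × 0.06 = 2.7.

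Suppose control across the whole omitted volume is truly 80%. Control in the pN0 neck alone is then 0.80 / (1 − fc) if failures in the two regions are independent, or 0.80 + fc by simple subtraction. The probability of at least 51 of 57 controlled on the pN0-only endpoint is:

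| f | c | Independence: pN0 control, P(success) | Subtraction: pN0 control, P(success) |
|---|---|---|---|
| 10% | 3% | 0.802, 4.9% | 0.803, 5.0% |
| 25% | 6% | 0.812, 7.0% | 0.815, 7.7% |
| 50% | 6% | 0.825, 10.7% | 0.830, 12.7% |
| 75% | 6% | 0.838, 16.1% | 0.845, 19.9% |

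**6. Cost of widening the primary event instead.** With pN0 control at 92% and cN0 failures also counted, control is 0.92 − fc by subtraction. At c = 6% and f = 25, 50 and 75% this is 0.905, 0.890 and 0.875. Power under the same rule falls from 83.1% to about 70%, 56% and 42%. Under independence it falls to 71.5%, 58.4% and 45.3%.

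**The case against.** **The primary endpoint is deliberate and consistent.** The abstract, the endpoint list, the outcome definition and the sample size section all restrict it to the pN0 neck. The 20% limit is justified as the risk that warrants treating one nodal basin, so pooling an undissected contralateral neck would set a larger volume against a per-basin limit. This stands. A reader might infer that the type I error is inflated or the power misstated. The document does not support that: for the hypothesis it states, exact alpha is 4.5% and power 83.1%. The probabilities in step 5 answer a different question, about the whole omitted volume.

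**Failures in the cN0 neck are captured.** A reader might infer that they go unrecorded. They do not: one secondary endpoint is dedicated to them and three others include them.

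**The affected group may be small.** Midline primaries should have bilateral dissection, pT3-T4 midline tumours with only an ipsilateral dissection are excluded, and the cN0 endpoint is described as applying to well-lateralized tumours. The 6% comes from a mixed oral cavity and oropharynx series in which 41% were N1 or N2, whereas trial patients with a unilateral dissection are pN0. This also stands, and is why the range extends down to almost no effect.

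**The discretion wording may be compatible with deletion.** The contour list uses similar language, and contours are fixed before randomization, so discretion could mean whether the cN0 neck is contoured at all. The outcomes section also points to a section of the full protocol that is not shown. This reading is possible and softens that part of the conflict. The text does not say it, however, and it leaves the clash between the volume definition and the contour list untouched.

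**The cN0 split is descriptive and only partly tied to arm.** That is correct, since uncontoured Arm 1 patients are also unirradiated. It remains uninformative about the effect of withholding radiation, because it mixes allocation with institutional practice.

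**Conclusion.** The concern holds in a limited form. The sections conflict on whether the cN0 neck is part of the randomized volume. If the deletion rule is followed, some Arm 2 patients lose radiation to a region that the primary endpoint does not cover and only secondary endpoints observe. The planned cN0 split is partly determined by arm.

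The size cannot be fixed from the article. Over an assumed 10-75% affected share and 3-6% cN0 failure, the chance of declaring success when the whole omitted volume truly fails at 20% is about 5-16% under independence, and up to 20% by subtraction, against 4.5%. At the low end the effect is negligible.

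It does not follow that the primary event must be redefined. That is a debatable trade-off with a substantial loss of power. Whether the cN0 neck should be irradiated is a clinical matter and is not judged here.

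**What to change.** 1. **Reconcile the text.** Make the volume definition, the contour list, the deletion rule with Table 1, and the outcomes section agree on whether a contoured cN0 neck is part of the randomized volume. The choice is the sponsor's clinical decision.
2. **Change the cN0 report.** Replace the split by radiation delivered with a report by arm within strata of the pre-randomization contour (cN0 neck contoured, yes or no).
3. **If the cN0 neck stays in the deleted volume,** keep the pN0-only primary endpoint and its stated power. Add a supportive Arm 2 estimate of failure anywhere in the omitted volume (CTVn60neg plus CTVn54neg as contoured before randomization), and limit the primary conclusion to the dissected pN0 neck.

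**Cost.** The changes are wording plus one data item, with no change in sample size. Contours are finalized before randomization, so the information exists. The mere presence of a CTVn54neg is not enough as the marker, because centres that treat the dissected pN0 neck to 54 Gy also place those levels in it; the item must record the cN0 neck itself. The by-arm comparison will be small: at an assumed 25% share, 30 × 0.25 = 7.5 patients in Arm 1 and 60 × 0.25 = 15 in Arm 2. It should be presented as descriptive.
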